### Study intervention

5As-based brief advice was offered to the intervention group participants by the study team who were trained by YO. This brief advice consisted of an individual session lasting approximately 5 min for each participant immediately after their consent had been obtained. The focus of the 5As was to enable the therapist know the immediate concern of each participant and to enable adequate support when the particular issues were raised during the group intervention sessions. The behavioral group intervention consisted of 6 sessions over 12 weeks and were led by 2 trained facilitators, followed by monthly group meetings from weeks 14 to 26. This program was adapted from the Royal Australian College of General Practitioners’ *Supporting Smoking Cessation Guide for Health Professionals* [19] and the World Health Organization’s *Strengthening Health Systems for Treating Tobacco Dependence in Primary Care* training package [20].

The topics that were explored during the group sessions include:
Introduction to the Program and Reasons to QuitBenefits of Quitting and Understanding Why We Smoke and Ways of QuittingWithdrawal Symptoms and Social SupportDealing with Stress and Anxiety and Coping with Depression due to withdrawalAssertiveness Training and Anger ManagementTobacco-Free Lifestyle and Dealing with High Risk Situations

#### Group session 1 (week 1)

On the first session, participants were introduced to the study program and specific components of the group behavioral intervention. Participants shared their expectations and experiences in their goal of tobacco cessation. The estimated time for group session 1 was 30–45 min.

#### Group sessions 2–6 (weeks 2–11)

Participants set their anticipated quit date on the 2nd week, which was their second session. During weeks 2 through 11, before the start of the session, feelings of participants were explored, the previous week’s self-reported tobacco consumption or cessation attempt was recorded. The topic of each week was explored first by lecture to explain the topic, and then group members took turns sharing their experiences on the topic.

#### Group sessions 7–9 (weeks 14–26)

Participants continued attending the CSAT outpatient and ward follow-up programs during this period. Behavioral group sessions 7–9 (weeks 14–26) were conducted once a month by the facilitators whereby each session was begun with a round of discussion on how participants were feeling about their cessation attempts, including any challenges they had experienced. The self-reported amount of tobacco used and quit attempts were documented. The study team also documented the challenges raised and tried to offer practical and supportive therapy for the challenges.

Summary of the group sessions and topics can be found in Table 1.

**Table 1 Tab1:** Group sessions and topics summary

Time Frame	Group sessions
After signed consent	5 As Ask- History of tobacco use Advice- On need to quit tobacco use, and inform on effects of tobacco use Assess- On readiness to quit tobacco use, if not ready use motivational skills to increase readiness Assist- Offer intervention support. Inform on behavioral coping skills and available pharmacotherapies Arrange- Arrange date, time and place of next session to introduce coping skills)
Session 1 (Week 1)	7. Introduction to the program and reasons to quit tobacco use
Session 2 (Week 3)	8. Benefits of quitting and understanding why we smoke and ways of quitting 9. setting quit date
Session 3 (Week 5)	10. Withdrawal symptoms and social support
Session 4 (Week 7)	11. Dealing with stress and anxiety and coping with depression
Session 5 (Week 9)	12. Assertiveness training and anger management
Session 6 (Week 11)	13. Tobacco-free lifestyle and dealing with high risk situations
Follow up sessions (Weeks 14–26)	14. Round of discussion on participants’ feelings, cessation attempts, challenges experienced, and how they coped 15. Documentation of self-reported quit attempts 16. Supportive therapy

### Baseline and follow-up assessments

During baseline, Age of first use, duration of use, amount used, mental illness managed, Fagerstrom test score, and other substances used were documented. During weeks 4, 12 and 26, Quit attempts made, amount currently being smoked and Cotinine test results were documented. During week 26, the WHOQOL questionnaire was re-administered.

Based on previous tobacco cessation intervention trials, it was assumed that those who did not report abstinence had positive cotinine results.

At the group assessments (Weeks 4, 12, and 26), participants who reported continued tobacco use abstinence and consented to a saliva test were tested using a nicotine cotinine strip (Devon Medical: Nicotine/tobacco test kit). The saliva tests were evaluated by the nurses working at the hospital who were blinded to treatment allocation and were not otherwise part of the study.

The summary of the follow-up assessment activities is reported in Table 2.

**Table 2 Tab2:** Baseline, Follow-up activities and Data to be collected summary

Follow-up time	Activity	Documentation
Week 0 (Baseline)	• Socio-demographic questionnaire • Fagerstrom test for nicotine dependence • WHO quality of life (QOL) instrument	• Age of first use, duration of use, amount used, mental illness managed, other substances used • Fagerstrom test score • WHO QOL score
Week 4	• Explored progress made and documented quit attempts • Focused on challenges experienced and how they were managed • Documented number of sticks currently smoked • Those reporting complete cessation and who gave consent for saliva testing, were then screened using cotinine test	• Quit attempts made • Amount currently being smoked • Cotinine test
Week 12	• Explored progress made and documented quit attempts • Focused on challenges experienced and how they were managed • Documented number of sticks currently smoked • Those reporting complete cessation and who gave consent, were screened using cotinine test	• Quit attempts made • Amount currently being smoked • Cotinine test
Week 26 (Final follow-up)	• Explored progress made and documented quit attempts • Focused on challenges experienced and how they were managed • Documented number of sticks currently smoked • Those reporting complete cessation, gave consent, then were screened using cotinine test • Administered WHO QOL instrument	• Recorded quit attempts made • Amount currently being smoked • Cotinine test • WHO QOL score

### Control group procedures

The control group was provided questionnaires to fill at the end of Weeks 4, 12, and 26. During the rest of the study, they continued receiving usual care, including clinical care at CSAT. After the conclusion of the study, the control group will be offered the group sessions that the intervention group received.

### Outcome measures

The study’s primary outcome was self-reported continuous tobacco use abstinence, biochemically verified, at Week 26. It was estimated that the intervention would increase tobacco cessation from the current rate of 15 to 35% [21]. While adjusting for 30% attrition rate, with a sample size of 48 per group, 96 participants would provide 80% power to detect this between-group difference with a two-sided alpha = 0.05.

Secondary outcomes assessed included cessation at Week 4 and 12, number of quit attempts, reduction in number of cigarettes used per day, and health-related quality of life measured at Week 26.

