### Sample size calculation [18]

The sample size necessary for comparing proportions includes: proportion *p*_*1*_ being the estimated proportion of study participants with improved health status after the intervention and *p*_*2*_ being the estimated proportion of study participants with improved health outcomes in the control group.

$$ n=\left(\frac{r+1}{r}\right)\;\frac{\left(\overline{p}\right)\;\left(1-\overline{p}\right)\;{\left({Z}_{\beta }+{Z}_{\alpha /2}\right)}^2}{{\left({p}_1-{p}_2\right)}^2} $$

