**Table Taba:** 

Ratio of intervention: controls (r)	1
Estimated proportion with improved outcomes in intervention group p_1_	35.0%
Estimated proportion with improved outcomes in control group p_2_	15.0%
Odds Ratio	3.05
Average of proportions (p_1_ + p_2_)/2	0.25
Power (1-α/2)	95%
Power (1-β)	80%
Sample size per group	37
Sample size per group after adjusting for 30% attrition rate	48
**Total sample size**	**96**

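### The protocol's own formula gives 74 per group, not 37, so the claimed 80% power is about 62% without loss and about 47% after the planned 30% attrition

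*Protocol article*

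**What the plan says.** The Sample size calculation section of the protocol article introduces a two-proportion formula ("The sample size necessary for comparing proportions includes" two proportions, *p*1 and *p*2) that carries the factor (r+1)/r. The table beneath it sets r = 1, p1 = 35%, p2 = 15%, a mean of 0.25 (row "Average of proportions (p_1_ + p_2_)/2") and 80% power. It reports 37 per group. In the row "Sample size per group after adjusting for 30% attrition rate" it reports 48, and it gives a total of 96.

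Outcome measures repeats the result for the primary outcome. It expects that "the intervention would increase tobacco cessation from the current rate of 15 to 35" per cent, and says that after adjusting for 30% attrition, "with a sample size of 48 per group, 96 participants would provide 80% power to detect this between-group difference", "with a two-sided alpha = 0.05". The Abstract reports that 50 per group were allocated.

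**The concern.** The formula, its inputs and its result are all printed, and they do not agree. The stated number per group is half of what the formula returns, and the prose then repeats it as a power claim for the primary outcome.

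Two smaller faults sit in the same table:

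- Attrition is handled by multiplying by 1.3, which does not protect against a 30% loss.
- The row labelled 1-α/2 shows 95%, which taken literally means alpha 0.10. The text says two-sided 0.05, for which 1-α/2 is 97.5%.

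What is at stake is how the result is read. The analysis tests at two-sided p < 0.05, and the article says the findings are to inform national and regional practice and policy. A reader told that the study had 80% power may take a non-significant result as evidence against the intervention, when the chance of detecting the planned effect was much lower.

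**Working it through.** **Inputs** (Sample size calculation and its table; Outcome measures): r = 1; p1 = 0.35; p2 = 0.15; difference 0.20; mean p̄ = 0.25, so p̄(1−p̄) = 0.1875; two-sided alpha 0.05, Z = 1.960; power 80%, Z = 0.8416; attrition 30%; stated 37, 48 and 96. Enrolled: 50 per group (Abstract).

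**1. The plan's formula with the plan's inputs**

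n = ((r+1)/r) × p̄(1−p̄) × (Zβ + Zα/2)² / (p1−p2)²

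n = 2 × 0.1875 × (0.8416 + 1.960)² / 0.04 = 73.58, so **74 per group**.

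**2. Where 37 comes from**

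Without the factor (r+1)/r = 2 the formula gives 73.58/2 = 36.79, which rounds up to the stated 37. The stated total also fits: 73.58 × 1.3 = 95.7, or 96. The likeliest explanation is that the formula's per-group number was taken as the total and split between the arms. The article shows no working, so this is inference. No figure below depends on it.

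**3. Other readings that might give 37**

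| Reading, 80% power | n per group |
|---|---|
| Pooled-variance (Fleiss) | 73 |
| Same with continuity correction | 83 |
| Unpooled variance | 70 |
| Arcsine | 71 |
| Alpha 0.10 two-sided, or 0.05 one-sided, plan's formula | 58 |

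None gives 37. The 95% in the 1-α/2 row therefore does not explain it either. The table's odds ratio of 3.05 does reproduce: (0.35/0.65)/(0.15/0.85) = 3.05.

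**4. Attrition**

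- As done: 37 × 1.3 = 48.1, stated as 48.
- As needed: 37/0.70 = 52.9, so 53.
- Left after 30% loss from 48: 48 × 0.70 = 33.6, below 37.
- Correct requirement: 74/0.70 = 105.7, so **106 per group, 212 in total**.

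**5. Power, by inverting the plan's formula**

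Power = Φ(0.20/√(2 × 0.1875/n) − 1.96)

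| n analysed per group | Situation | Power |
|---|---|---|
| 33.6 | 48 less 30% | 47% |
| 35 | 50 less 30% | 49% |
| 37 | the table's unadjusted figure | 51% |
| 48 | planned, no loss | 62% |
| 50 | enrolled, no loss | 64% |
| 74 | formula's requirement | 80% |

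Exact enumeration of the uncorrected chi-squared test gives 50% at 34, 63% at 48, 65% at 50 and 81% at 74. Fisher's exact test gives 37% at 34 and 54% at 48.

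**6. Sensitivity case: lost participants counted as smokers (an assumption)**

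Baseline and follow-up assessments says "it was assumed that those who did not report abstinence had positive cotinine results". That sentence does not name dropouts, so applying it to them is one reading. Suppose also that 15% and 35% are rates among completers and that loss is unrelated to quitting. The rates become 0.35 × 0.70 = 24.5% and 0.15 × 0.70 = 10.5%. Power is then about 44% with 48 per group and 45% with 50.

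**7. Detectable effect at 80% power, control rate 15%**

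- Intervention rate 40%: 2 × 0.275 × 0.725 × 7.849/0.25² = 50.1. So 50 per group detects about 25 points.
- Intervention rate 46%: 2 × 0.305 × 0.695 × 7.849/0.31² = 34.6. So 35 per group detects about 31 points.

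**The case against.** The arithmetic of 74 against 37 is not in dispute, and the error is not an artefact of text extraction, because the prose repeats 48, 96 and 80%. The fair objections concern scope.

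- **The 47% is conditional.** It assumes that only completers are analysed. If everyone enrolled is analysed, and 15% and 35% already describe everyone enrolled, attrition does not shrink n and power stays at 62% to 64%. The article does not say which population the rates describe. This stands as a reason to give both figures. It does not rescue the 80%, which is claimed after adjustment for 30% attrition and is missed either way.
- **The smokers-by-default case goes beyond the text.** This stands. It is labelled above as an assumption, and the conclusion does not rest on it.
- **The attrition step and the 1-α/2 label are minor.** This stands. The wrong inflation costs 5 per group (53 − 48), while the halving costs 37 (74 − 37). The label is a slip that the prose contradicts plainly.
- **No passage says a null result would be read as no effect, and the article admits the limits of non-randomised allocation.** True, but that admission concerns confounding. It does not warn the reader about power.
- **Putting 74 and 106 into the table would suggest a target that was never set.** This is a reasonable point about presentation, and the correction below allows for it.

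**Conclusion.** The concern holds. The only sample size justification for the primary outcome is wrong by a factor of two on its own formula and inputs, and the 80% power claim is false as written. Power for 15% against 35% at two-sided 0.05 is 62% (48 per group) to 64% (50 per group) with no loss, and 47% to 49% if 30% are lost and only completers are analysed. Under the further assumption that lost participants count as smokers, it is 44% to 45%.

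All these figures treat participants as independent. Allocation was in blocks of 10, and the intervention was delivered in groups. Any correlation within those groups would lower power further. The article gives no intraclass correlation, so this is not quantified.

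**What to change.** - In the Sample size calculation table, state that the formula gives 74 per group, and 106 per group (212 in total) with 30% attrition by n/(1 − 0.30). Keep 48 per group and 96 in total only as a record of the target used, and say that they do not follow from the formula. Correct the 1-α/2 row to 97.5%.
- In Outcome measures, replace the 80% claim with the power of the 100 enrolled: about 64% without loss and about 49% with 30% loss, or about 45% if lost participants are counted as smokers, stated as an assumption.
- State the detectable difference at 80% power: about 25 points without loss and about 31 points with 35 per group.
- Report the week 26 risk difference with its 95% confidence interval, and do not interpret non-significance as lack of efficacy.

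Current status gives follow-up as complete, so this is a correction of text and table, carried into the results report. It needs no extra participants or data. The cost is a less favourable power statement.

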**Methods/design:**

One hundred tobacco users with mental illness who were part of an outpatient mental health program in Nairobi, Kenya were recruited and allocated into intervention and control groups of the study (50 users in intervention group and 50 users in control group). Participants allocated to the intervention group were invited to participate in 1 of 5 tobacco cessation groups. The intervention group received the 5As (Ask, Advise, Assess, Assist and Arrange) and tobacco cessation group behavioral intervention, which included strategies to manage cravings and withdrawal, stress and anxiety, and coping with depression due to withdrawal; assertiveness training and anger management; reasons to quit, benefits of quitting and different ways of quitting. Individuals allocated to the control group received usual care. The primary outcome was tobacco cessation at 24 weeks, measured through cotinine strips. Secondary outcomes included number of quit attempts and health-related quality of life.

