### Inclusion criteria

18 years of age and above.History of tobacco use for more than 6 months.A Fagerstrom score of 6 and above, which is a threshold consistent with dependence [17].Currently on outpatient follow up treatment for a diagnosed mental health condition.Willing to be part of the study for 6 months.

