### Data management and analysis

Data were collected using structured questionnaires and entered into a secure, password-protected database. The hard copy data forms have been stored in a lockable cabinet in lockable office during collection, data entry, analysis, and after study completion. Upon completion of data entry, 20% of hard copy forms will be compared with the entered data to identify systematic or random errors and corrections and repeated data entry will be made appropriately, including 100% recheck if a > 2% error rate is detected.

Sociodemographic characteristics of the study participants, such as age, gender, residence, education level, occupation and perceived health status will be reported. We will also report participants’ health-related quality of life at baseline using the WHOQOL-100 and document participants’ primary mental health disorder. The kind of tobacco product under use, daily amount of tobacco consumption, duration of use, and age of initiation to tobacco will also be described. Using the Fagerstom test, we will determine nicotine dependency and describe intent to quit use of tobacco products. Data on any other substance use such as alcohol, bhang and miraa, including duration of use, will also be reported.

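### Entry is open to users of any tobacco product, but the secondary reduction outcome counts cigarettes, so smokeless-only users cannot show a reduction and a switch to a smokeless product scores as a full one

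*Protocol article*

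**What the plan says.** **Population.** Under Inclusion criteria, the tobacco criterion is "History of tobacco use for more than 6 months", together with "A Fagerstrom score of 6 and above, which is a threshold consistent with dependence". Neither criterion names cigarettes. The abstract's Methods/design paragraph describes the participants as "One hundred tobacco users with mental illness".

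**Product type.** Data management and analysis expects products to differ: "The kind of tobacco product under use, daily amount of tobacco consumption, duration of use, and age of initiation to tobacco will also be described".

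**Outcome.** Outcome measures lists among the secondary outcomes "reduction in number of cigarettes used per day, and health-related quality of life measured at Week 26"; the first of these two is the consumption outcome. The primary outcome in the same section is abstinence from tobacco at Week 26 with biochemical verification, which is not tied to one product.

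**Follow-up data.** Baseline and follow-up assessments states for Weeks 4, 12 and 26 that "Quit attempts made, amount currently being smoked and Cotinine test results were documented". The activity column of Table 2 says "Documented number of sticks currently smoked" at each of the three visits. At baseline the same section uses the broader term of amount used.

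**Other records.** The descriptions of group sessions 2–6 and 7–9 say that participants' own reports of tobacco consumption were noted. Those sessions were held for the intervention arm only. Control group procedures describes questionnaires at Weeks 4, 12 and 26 and otherwise usual care.

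**The concern.** The unit narrows between enrolment and follow-up: people enter as tobacco users, baseline covers tobacco of any kind, and the reduction outcome then counts cigarettes. Two kinds of participant get a score that does not describe their tobacco use, even if the plan is followed exactly. In a trial about tobacco cessation, replacing cigarettes with another tobacco product could then appear as benefit on this outcome, and real change in smokeless users could not appear at all. What is at stake is the meaning of one secondary result, not the trial's main conclusion.

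**Working it through.** The plan gives no figure for this outcome: no expected reduction, no variance and no product mix. There is nothing to reproduce, so the check applies the definition to each type of participant.

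**Step 1: score each type.** Let B be cigarettes per day at baseline and F cigarettes per day at follow-up. The outcome is B − F, or (B − F)/B if expressed as a proportion. The 20 a day below is only an example.

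| Participant | B | F | Score | Still using tobacco? |
|---|---|---|---|---|
| Cigarette smoker who stops all tobacco | 20 | 0 | 20 − 0 = 20, or 20/20 = 100% | No |
| Cigarette smoker who switches to a smokeless product | 20 | 0 | 20 − 0 = 20, or 20/20 = 100% | Yes |
| Smokeless-only user who stops | 0 | 0 | 0 − 0 = 0; proportion undefined | No |
| Smokeless-only user who continues | 0 | 0 | 0 − 0 = 0; proportion undefined | Yes |

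The outcome cannot separate the first row from the second, or the third from the fourth.

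**Step 2: does cotinine correct it?** Under Baseline and follow-up assessments, strips go to participants who report abstinence and agree to the saliva test. A switcher who says that tobacco use continues is not tested. One who claims abstinence and tests positive fails the abstinence outcome, but no stated rule carries the strip result over to the cigarette count. Cotinine therefore protects the primary outcome and not this one.

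**Step 3: can other records fill the gap?** The session records refer to tobacco consumption generally, but only for the intervention arm. For the control arm, the article describes the Week 4, 12 and 26 data only as sticks or amount smoked. As described, no amount covering all products exists in both arms.

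**Step 4: effect on an arm mean, in symbols.**
- If a share f of an arm smoked no cigarettes at baseline, and m is the mean reduction among the rest, the arm mean is f × 0 + (1 − f) × m = (1 − f)m. This pulls the mean towards zero.
- If a share s of an arm switches product from an average of c cigarettes per day, s × c of the arm's mean reduction reflects switching and not less tobacco use. This raises the mean.

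The documents give no value of f, s or c for either arm. The two effects work in opposite directions, so neither the size nor the sign of the net error in the comparison between arms can be derived. If f = 0, the first effect vanishes (1 − 0 = 1); the second can remain even if everyone smoked cigarettes at baseline.

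**The case against.** **Few participants may be affected.** Entry also requires a Fagerstrom score of at least 6, and the section on that test discusses it in terms of smokers. The article names no smokeless user. The share without cigarettes could be close to zero. This stands, and it is why no size is claimed. It does not remove the switching problem.

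**Other smoked products may be captured.** Amount smoked is wider than cigarettes. A reader might infer that no user of another product can show a reduction; the documents do not support that. The strict statement holds for exclusively smokeless users.

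**The main result is safe.** The primary outcome is abstinence from tobacco, verified by cotinine, so a change of product is not cessation under its definition. A reader might infer that the cessation finding is compromised; it is not.

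**Unequal error between arms is not shown.** A reader might infer that the intervention steers its arm towards cutting down or switching, and so inflates the benefit. The listed topics concern quitting, withdrawal, coping and a tobacco-free lifestyle; none promotes another product. Table 1 places the six core sessions two weeks apart, so an argument from weekly coaching also fails. What stands is narrower: wider consumption data are described in one arm only.

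**The forms are not shown.** Table 2 is a summary, and the questionnaires may have asked about other products. That is possible, and the fix allows for it. But the article itself states the outcome definition, and that definition says cigarettes.

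**Conclusion.** The point holds as a mismatch between the enrolled population and the unit of one secondary outcome. It follows from the article's own wording: exclusively smokeless users cannot register a reduction, and smokers who switch to a smokeless product register a full one. It rests on reading the outcome as cigarettes, as written, and on the entry criteria not being limited to cigarette smokers.

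Its size is unknown, because the product mix and the frequency of switching are not given, and it may be small. No direction of bias between arms is claimed. The primary outcome does not have this defect. The correction is worth making because it is nearly free and can still be made: Current status reports that follow-up ended on 28 June 2019, while the analysis is still written in the future tense.

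**What to change.** 1. Define the analysis set for this outcome as participants who smoked cigarettes at baseline, using the kind of product already recorded, and analyse change in cigarettes per day in that set by arm.
2. Report users of other products separately and descriptively, with their number in each arm.
3. State in the outcome definition and in the report that the result concerns cigarettes and is not a reduction in total tobacco use.
4. If the Week 4, 12 and 26 forms captured amounts of all products in both arms, report product switching by arm beside the cigarette result. If they did not, state that as a limitation; the items can no longer be added, and the session records of one arm should not stand in for them.

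A rule that scores every switcher as unchanged is not advised: it would also erase a genuine large fall in cigarettes in someone who occasionally uses another product.

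The cost is a change of wording and of analysis set, with slightly fewer participants in this secondary analysis. No new data are needed.
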